## Methods

### Study design

This study is a prospective clinical investigation designed to generate safety data. It is an open-label, phase I trial designed to determine the safety and tolerability of intradermal administration of patient-specific scFv-CCL20 DNA vaccine in patients with asymptomatic LPL. Patients will receive a series of 3 vaccinations at 4-week intervals (weeks 0, 4 and 8). The 2 pre-defined dose levels – Cohort 1 (500 μg DNA vaccine) and Cohort 2 (2500 μg DNA vaccine) – were chosen based on the pre-clinical experience [24, 25].

All patients will either undergo bone marrow aspiration of 10 ml or lymph node harvest prior to starting treatment to obtain cells to prepare their vaccine. Once the vaccine for a given patient is available, he or she will receive 3 doses of DNA vaccine encoding autologous lymphoma scFv- human CCL20 (MIP-3α) fusion protein.

Enrollment to Cohorts 1 and 2 will follow a standard 3 + 3 statistical design, and will thus require a maximum of 12 patients, and shall be staggered to ensure no patient is administered the vaccine until any previously exposed patient has completed a minimum of 48 h of safety follow-up after receiving the first DNA vaccine administration. Prior to advancing dose levels, a cohort summary will be completed and submitted to the IND office medical monitor for review and approval to proceed to the next cohort.

If patients have progressive disease that requires chemotherapy or radiotherapy treatment before or while receiving vaccination, vaccination will either not begin or will be stopped, and the patient will be taken off study. Patients will be vaccinated intradermally and the injection sites will be rotated between the thighs. Patients will be observed in CTRC for 2 h after vaccine administration; vital signs will be taken every 15 min during the first hour and every 30 min during the second hour. The use of non-steroidal anti-inflammatory drugs (NSAIDs) and/or steroids should be avoided during the vaccination. Should NSAIDs or steroids be required for unrelated medical conditions for a course exceeding 2 weeks, the patient will be taken off the study. Patients will receive a list of common aspirin containing products to avoid at the time of study entry. Any local skin reactions will be carefully noted and scored for erythema, induration, pain and disruption of the barrier surface.

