### Patients

Adult (age ≥ 18 years) patients with asymptomatic phase, previously untreated LPL with surface IgG, IgA or IgM phenotype tissue diagnosis and a monoclonal heavy and light chain as determined by flow cytometry who are able to provide informed consent will be eligible for this study [30]. All primary diagnostic lymph node and/or bone marrow biopsies will be reviewed at the University of Texas M.D. Anderson Cancer Center (UTMDACC). Patients must provide a lymph node sample of at least 1.5 cm in the long axis, or a bone marrow aspiration sample providing at least 5 million CD20 and/or CD38+ cells (approximately 10 ml). Patients mush also have a good performance status (ECOG 0 or 1), and be able to attend clinic for adequate follow-up for the period that the protocol requires. In addition patients must have adequate kidney and liver function, defined by serum creatinine ≤1.5 mg/dl and a creatinine clearance ≥ 30 ml/min, and total bilirubin ≤1.5 mg/dl unless believed secondary to Gilbert’s disease, and AST/ALT ≤2 x upper limit of normal.

Female subjects must be either post-menopausal or surgically sterilized or willing to use an acceptable method of birth control (i.e., a hormonal contraceptive, intra-uterine device, diaphragm with spermicide, condom with spermicide, or abstinence) for the duration of the study and for 30 days after the last vaccination has been administered. Male subjects should agree to use an acceptable method for contraception for the duration of the study.

Patients will be excluded from the study if they have HIV, Hepatitis B and/or Hepatitis C infection; a previous history of malignancy within the last 5 years except curatively treated squamous or basal cell carcinoma of the skin or curatively treated carcinoma in-situ of other organs; have any medical or psychiatric condition that in the opinion of the principal investigator would compromise the patient’s ability to tolerate this treatment; have New York Heart Association Class 3 or 4 disease; have a history of autoimmune diseases except for Hashimoto’s thyroiditis; or have a positive ANA and/or anti-dsDNA antibodies. Additionally, pregnant or lactating females are excluded.

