All patients will be registered in the Clinical Oncology Research System (CORe). All patients who have asymptomatic LPL will be seen by members of the UTMDACC Department of Lymphoma and Myeloma, and tracked by the research nurse/study coordinator in charge of this study. Participation on this protocol will be discussed with patients deemed eligible. Formal screening for eligibility will occur if informed consent is received. The informed consent document is included in the Supplementary Data. For eligible patients not enrolled on the study, a Health Insurance Portability and Accountability Act (HIPAA) compliant pre-enrollment and enrollment log will be maintained in CORe to track reason(s) for lack of enrollment. The patient’s entry date on protocol will be the day the patient is registered in CORe. The treatment start date will be the day the first dose of vaccine is administered to the patient.

Patients will be removed from protocol for any of the following reasons: adverse event(s) occur that in the judgment of the investigator, may cause severe or permanent harm or which rule out continuation of study drug; the patient declines further therapy, experiences progression of LPL that requires initiation of systemic therapy to control symptoms, or has an inadequate number of biopsy cells (< 1.0 × 10^9^) for vaccine manufacture or there is an unforeseen vaccine manufacturing failure. Additionally a patient will be removed from protocol if it is deemed in their best interest, in which case the Principal Investigator should be notified, and the reasons for withdrawal should be noted in the flow sheet.

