### Statistical plan

DLT is defined as follows: ≥ grade 2 allergic reaction, ≥ grade 2 autoimmune reaction and any grade 3 or 4 toxicity except for fever, grade 4 fever which subsequently requires 50% dose reduction. Applying the 3 + 3 design [35], the first cohort of 3 patients will be treated at dose level 1 and evaluated for DLT at the end of the first cycle (4 weeks). Following the standard 3 + 3 design, the MTD is defined as the highest dose level in which 6 patients have been treated with less than 2 instances of DLT [35]. Given 2 predefined dose levels, it is anticipated that up to 12 eligible patients are required for this dose-finding phase I trial.

If greater than 1 out of 3 patients or 1 out of 6 patients experience DLT at the lower dose level, this dose will be considered too toxic and the protocol will be stopped.

Toxicity type and severity will be summarized by frequency tables.

The secondary endpoint of immune response will estimated using the intent-to-treat population. Immune response will be defined as at least a three-fold rise in the frequency of tumor-reactive precursor T-cells in the 12 weeks post-vaccine PBMC sample compared with the pre-vaccine sample, or a minimum precursor frequency of 1 in 80,000 cells post vaccination if the precursor frequency in the pre-vaccine sample is zero.

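### Immune response is to be estimated in the intent-to-treat population, which on its ordinary reading counts registered patients who never receive a vaccine and so cannot respond

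*Protocol article*

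**What the plan says.** The Statistical plan fixes the analysis set for the secondary endpoint: "The secondary endpoint of immune response will estimated using the intent-to-treat population". It defines response as at least a three-fold rise in tumor-reactive precursor T cells "in the 12 weeks post-vaccine PBMC sample compared with the pre-vaccine sample". Where the pre-vaccine frequency is zero, it requires a minimum frequency of 1 in 80,000 cells after vaccination.

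The Patients section separates two dates. The patient's "entry date on protocol will be the day the patient is registered in CORe", whereas "The treatment start date will be the day the first dose of vaccine is administered to the patient". The Study drug section gives 12 months for preparing each patient-specific vaccine.

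The article names three ways to leave before any dose:

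- **Progression** needing chemotherapy or radiotherapy before or during vaccination, after which "vaccination will either not begin or will be stopped, and the patient will be taken off study" (Study design).
- **Too few cells**: the patient "has an inadequate number of biopsy cells" for manufacture (Patients).
- **Manufacturing failure**: "there is an unforeseen vaccine manufacturing failure" (Patients).

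The Objectives section states what the endpoint is for: assessing whether the vaccine can generate tumor-specific immune responses.

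**The concern.** Both response criteria need a sample taken after vaccination, so a patient who is never vaccinated cannot meet either. If the analysis set is everyone registered, such a patient is a certain non-responder for a reason unrelated to the vaccine's activity. The rate would then mix three things: immunogenicity, manufacturing yield, and progression while waiting for the product. Only the first is the stated objective.

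The usual reason for an intent-to-treat set is to protect a randomised comparison. This trial is open-label and non-randomised, so there is none to protect. The same section already counts treated patients when it defines the MTD.

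What is at stake is the descriptive response rate, and the informal comparison between dose levels if undosed exits differ between cohorts. The article expects stronger T-cell responses at the higher dose, so readers will look at that comparison.

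**Working it through.** **Step 1: the plan's own figure.** Two dose levels with up to 6 treated patients each give 2 × 6 = 12, which matches the stated maximum. No test, power or threshold is given for immune response, so there is nothing else to reproduce.

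**Step 2: can undosed patients be on study?** Entry is registration and treatment start is the first dose. Too few biopsy cells and manufacturing failure are listed as reasons for removal from protocol. Both arise before dosing, and a patient can be removed only after entering. Registered but undosed patients are therefore a category that the article foresees.

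**Step 3: size of the dilution.** Let R be the number of responders, D the number of dosed patients and U the number registered but undosed. All responders are among the dosed, so

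R/(D + U) = (R/D) × D/(D + U).

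The factor D/(D + U) does not depend on R. U is not stated anywhere, so the values below are assumptions.

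| Setting | U = 0 | U = 1 | U = 2 | U = 3 |
|---|---|---|---|---|
| 12 dosed, undosed extra | 1 | 12/13 = 0.92 | 12/14 = 0.86 | 12/15 = 0.80 |
| Undosed counted within 12 | 1 | 11/12 = 0.92 | 10/12 = 0.83 | 9/12 = 0.75 |
| One cohort, 6 dosed, undosed extra | 1 | 6/7 = 0.86 | 6/8 = 0.75 | – |
| Undosed counted within 6 | 1 | 5/6 = 0.83 | 4/6 = 0.67 | – |

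**Step 4: example.** Three responders among 6 dosed patients is 3/6 = 50.0%. With one undosed patient in the denominator it is 3/7 = 42.9%. If this happened in one cohort only, two cohorts with the same rate among dosed patients would read 42.9% and 50.0%.

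**Step 5: the same check by share of registered patients.** To have 12 dosed patients when 10%, 20% or 30% of those registered are never dosed (assumed), registration must reach 12/0.9, 12/0.8 or 12/0.7, rounded up to 14, 15 or 18. Six responders, 6/12 = 50% of the dosed, then read 6/14 = 43%, 6/15 = 40% or 6/18 = 33%.

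**The case against.** The strongest reply is that the article does not define intent-to-treat. Analysis sets are commonly defined in the full protocol or analysis plan, and a definition as dosed patients would remove the problem. The term also has no settled meaning in a trial without randomisation, and the article's own sample-size count rests on treated patients. This stands as a limit: all registered is an assumption. It does not dispose of the point. The article names a population, dates entry at registration and speaks of removing undosed patients from the protocol, so the broad reading is the natural one and it fits the endpoint badly.

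A second reply is that, for an individually manufactured product, counting failures to manufacture gives a conservative rate for the whole strategy. That is a legitimate quantity, but it is not the stated objective, and reporting undosed patients separately preserves the information.

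A third is that nothing turns on the rate. The endpoint is secondary, called hypothesis-generating and given no decision rule. The exact 95% interval for 3/6 is about 12% to 88%, far wider than the shift to 42.9%. This stands, and it keeps the point minor.

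A reader might go further in two ways that the documents do not support:

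- **That the reported rate will be too low.** No number of undosed exits is given, and the Discussion reports the first 6 patients as enrolled and treated, which shows no such exit.
- **That undosed exits are built in**, because the marrow entry requirement of 5 million cells lies far below the removal limit of 1.0 × 10^9. The first figure counts CD20 and/or CD38+ cells and the second counts biopsy cells. These may be different populations, so the comparison establishes nothing here and the point does not rely on it.

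**Conclusion.** The point holds as a minor one. On the ordinary reading, the named population includes patients who cannot meet the endpoint, and each of them lowers the rate for a reason unrelated to the vaccine. With one to three undosed patients, the whole-trial factor runs from 0.92 down to 0.75. With one or two in a single cohort, it runs from 0.86 down to 0.67.

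This rests on two assumptions: that intent-to-treat means all registered patients, and that at least one patient leaves undosed. If either fails, the factor is 1 and nothing changes. The MTD and the dose-escalation rule are unaffected in every case.

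**What to change.** Replace the population sentence in the Statistical plan with wording such as:

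> Immune response will be estimated, by cohort, in all patients who received at least one vaccine dose. A dosed patient without a 12-week sample counts as a non-responder. Patients registered but never dosed will be reported separately, with the reason.

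The treatment start date already identifies the dosed set. Counting a missing sample as non-response keeps the estimate conservative about dropout after dosing.

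The cost is this one change of wording, with no added patients, visits or samples. The downside is that the headline rate no longer reflects feasibility, which the separate report covers. If the full plan already means dosed patients, the change only makes that explicit.

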#### Assay of precursor frequency of tumor-specific cytotoxic T-lymphocytes

The precursor frequency of tumor-specific cytotoxic T-lymphocytes will be determined by modified interferon gamma (IFNγ) ELISPOT assay as described previously [32]. A three-fold rise in the frequency of tumor-reactive T cell precursors in the post-vaccine PBMC sample compared to the pre-vaccine sample will be considered positive, with a minimum precursor frequency of 1 in 80,000 cells if the precursor frequency in the pre-vaccine sample is zero [33].

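### The 1-in-80,000 minimum for a T-cell response applies only at a zero baseline, so if more than 240,000 cells are tested a trace baseline faces a lower bar than none

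*Protocol article*

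**What the plan says.** The protocol article states the responder rule twice.

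- **Statistical plan:** "Immune response will be defined as at least a three-fold rise in the frequency of tumor-reactive precursor T-cells in the 12 weeks post-vaccine PBMC sample", measured against what was found before vaccination. A second route to a response is then added in these words: "or a minimum precursor frequency of 1 in 80,000 cells post vaccination if the precursor frequency in the pre-vaccine sample is zero".
- **Assay of precursor frequency of tumor-specific cytotoxic T-lymphocytes:** "A three-fold rise in the frequency of tumor-reactive T cell precursors in the post-vaccine PBMC sample compared to the pre-vaccine sample will be considered positive". The absolute minimum again appears only as a rider for patients who start from nothing: "with a minimum precursor frequency of 1 in 80,000 cells if the precursor frequency in the pre-vaccine sample is zero".

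Both places attach the absolute minimum to a zero baseline and to nothing else. Neither sets a minimum for a patient whose baseline is above zero, and neither says that a very low baseline is to be read as zero. The frequency "will be determined by modified interferon gamma (IFNγ) ELISPOT assay as described previously". The article gives neither the number of cells tested per sample nor a detection limit.

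The rule defines a secondary endpoint: "The secondary endpoint of immune response will estimated using the intent-to-treat population". On numbers, "it is anticipated that up to 12 eligible patients are required for this dose-finding phase I trial".

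**The concern.** A minimum is needed at a zero baseline because no ratio can be formed there. As written, however, it sets a bar that some patients with a non-zero baseline do not have to reach. Take two patients who both reach 5 per million after vaccination. The one who started at 1 per million is a responder (a five-fold rise). The one who started at zero is not (5 is below 12.5). The article gives no reason for ranking them that way.

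The low bar also applies where counts are smallest. A three-fold rise from one spot is a rise to three, which sampling variation alone can produce. With at most 12 patients, one or two such calls would visibly move the reported response proportion.

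**Working it through.** The plan gives no figure to reproduce here, so I applied the rule directly.

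**Inputs from the article:** fold criterion 3; minimum 1/80,000, only if the pre-vaccine frequency is zero; at most 12 patients.

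**Assumptions:** the number of cells tested per sample, N, is the same before and after vaccination and is varied because it is not stated. Spot counts are independent Poisson with mean λ = N × true frequency, and there is no true change.

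**Step 1: where the bars cross.** The required post-vaccine frequency is T(0) = 1/80,000 = 12.5 per million for a zero baseline and T(b) = 3b for b > 0. T(b) < T(0) when b < 1/(3 × 80,000) = 1/240,000.

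| Baseline | Required after vaccination | Relative to the zero-baseline bar |
|---|---|---|
| 0 | 1/80,000 | 100% |
| 1/1,000,000 | 1/333,333 | 24% |
| 1/500,000 | 1/166,667 | 48% |
| 1/300,000 | 1/100,000 | 80% |
| 1/240,000 | 1/80,000 | 100% |
| 1/200,000 | 1/66,667 | 120% |

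**Step 2: when such a baseline can be observed.** The smallest non-zero result is one spot, a frequency of 1/N, and it needs three spots afterwards. A zero baseline needs N/80,000 spots, rounded up.

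| Cells tested (assumed) | Spots needed from zero | Spots needed from one |
|---|---|---|
| 80,000 | 1 | 3 |
| 240,000 | 3 | 3 |
| 250,000 | 4 | 3 |
| 400,000 | 5 | 3 |
| 1,000,000 | 13 | 3 |

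The inversion appears only when N exceeds 240,000.

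**Step 3: false responses with no true change.** Let m be N/80,000 rounded up.

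- As written: P(pre = 0) × P(post ≥ m) + Σ over k ≥ 1 of P(pre = k) × P(post ≥ 3k).
- Minimum for all: Σ over k ≥ 0 of P(pre = k) × P(post ≥ the larger of 3k and m).

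Worked case, N = 1,000,000 and 3 per million, so λ = 3 and m = 13:

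- k = 1: 0.149 × 0.577 = 0.0862
- k = 2: 0.224 × 0.0839 = 0.0188
- k = 3: 0.224 × 0.0038 = 0.0009
- k = 0 and k ≥ 4: negligible

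The sum is 0.106. With the minimum for all it is about 0.00001.

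| Cells tested (assumed) | As written, at 1, 2, 3, 4, 5 per million | Minimum for all, over the same range |
|---|---|---|
| 1,000,000 | 3.0, 9.2, 10.6, 9.2, 7.2% | at most 0.09% |
| 400,000 | 0.2, 1.8, 4.6, 7.6, 9.9% | 0.01–2.6% |
| 240,000 | 0.2, 1.2, 3.1, 5.5, 8.0% | identical |

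The frequencies in this table are true ones. At 5 per million the true value lies just above the crossover of 1,000,000/240,000 = 4.17 per million, but the observed baseline can still fall below it.

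**Step 4: what the change leaves untouched.** At higher true frequencies, near 10 per million, the false-response chance reaches about 26% at 80,000 cells and 14% at 240,000 under either rule. At 400,000 cells it still reaches about 7% with the minimum applied to all.

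**The case against.** The strongest reply is that the inversion may never occur. The article leaves the assay method and the positivity rule to cited work. If 1 in 80,000 is close to the smallest frequency the assay resolves, no baseline below 1 in 240,000 can be seen, and the clause does only what a zero denominator requires. This stands as a limit on the point: the documents neither confirm nor exclude it. The blood drawn for PBMC under Study procedures, 30 to 60 ml per time point, makes larger cell inputs possible but does not show that they are used. It does not remove the point, because the article fixes the definition in words that allow the inversion. If the assay cannot resolve such baselines, the correction changes no result.

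A second reply is that chance responses are a wider problem than this clause. That is correct, as step 4 shows. The correction removes the inversion, not chance responses in general.

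A reader might also infer two stronger things that the documents do not support:

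- **That about 1.3 of 12 patients would be false responders** (12 × 0.106), with a 74% chance of at least one (1 − 0.894^12). This needs all 12 patients near 3 per million and 1 million cells tested. At 1 per million and the same input, the chance of at least one is about 30% (1 − 0.9703^12). At 400,000 cells and 1 per million, the per-patient figure is only 0.2%.
- **That the responder count could steer the phase 2 dose.** The Risk/benefit assessment makes the MTD the primary endpoint, and the Statistical plan bases it on DLTs. The Discussion links the dose likely to go forward to expected tolerability. No stated decision uses the responder count.

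**Conclusion.** The point holds, conditionally. From the text alone, the minimum is tied to a zero baseline in both sections, and the required level is lower for any non-zero baseline below 1 in 240,000. Whether patients would be misclassified depends on more than 240,000 cells being tested per sample, which is an assumption. The false-response figures rest further on the Poisson model and on true frequencies of 1 to 5 per million; they are illustrations, not forecasts for this trial.

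The consequence is limited to the responder count of a secondary endpoint that the article itself describes as hypothesis-generating with limited power. The MTD, the DLT rules and the sample size are unaffected. It is still worth correcting, because this is the only responder definition in the Statistical plan and the correction is short.

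**What to change.** Put the same sentence in the Statistical plan and in the assay section: for every patient, a response is a post-vaccine precursor frequency of at least three times the pre-vaccine frequency and at least 1 in 80,000. At a zero baseline the first condition is met automatically and the second decides, so no separate clause is needed. Nothing changes for baselines of 1 in 240,000 or higher. Report each patient's pre- and post-vaccine frequencies as continuous values beside the responder count.

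The cost is one sentence in two places, with no new samples or assay work. The downside is small: a genuine rise that stays below 1 in 80,000 no longer counts as a response, though it remains visible in the continuous data. The number of cells tested per sample and the detection limit should be stated alongside, so that a reader can judge how much of any response proportion chance could explain; the new sentence does not settle that.
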